## Results

The research was funded in January 2020, and data collection started in January 2022, with a projected data collection completion date of August 2024. The number of participants that have consented at the point of manuscript submission is 66. It is expected that all data analysis will be completed and results published by the end of 2024.

## Discussion

### Primary Findings

HC use is highly prevalent among servicewomen [41]. Military training is physically arduous, particularly for women [42], who experience a greater risk of musculoskeletal injuries and stress fractures than men [43]. Previous studies have shown that HC choice may inhibit skeletal adaptation to military training [24,44] and may increase stress fracture risk [45]. These studies have combined progestogen-only methods and do not report effects on muscle and soft tissue, which are limitations this study aims to address. There are limited data on the influence of contraceptives on musculoskeletal health and performance. We aim to characterize the musculoskeletal health and function of regularly menstruating women across the menstrual cycle and compare the outcomes of women using different types of HCs. These data are principally needed to understand the potential musculoskeletal injury risk (or protection) from the use of HCs in female military personnel, but the findings will have applications across wider physically active occupational groups and for female athletes and may be incorporated into public health guidance for the general population. Understanding the effects of estrogens and progesterone or progestogen on musculoskeletal health and performance will inform contraceptive choices for women and improve our understanding of the musculoskeletal risks of contraceptive use and the menstrual cycle stage.

### Strengths

Through the use of strict eligibility criteria, we will be able to control for factors that may affect the study outcomes, including age, BMI, pregnancy and postpartum status, bone injury, length of HC use, pathologies affecting hormonal functions (eg, thyroid disease), and specific HC type. This is one of the first studies of its kind to investigate such a broad range of HCs and consider all 4 phases of the menstrual cycle for physical performance assessment.

### Limitations

The cross-sectional study design prevents standardized and controlled administration (frequency and dose) of HCs in the COCP group, and the self-selection of hormonal contraception across groups may introduce selection bias. A randomized control trial design of HC interventions was not considered feasible for this research due to the length of time needed to elucidate meaningful effects, the impact on lifestyle and health care for participants, and the invasive procedures for the administration of LARCs. Functional movement—visually assessed from the location of the midpoint of the knee and ankle using video footage—may also be subject to observer bias; this bias will be minimized by using a single trained observer. Investigators will also be involved in the testing of all study participants and will not be blinded to HC groups.

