## Methods

### Recruitment

Biochemical markers of bone and calcium metabolism and measures of musculoskeletal health and performance will be obtained in physically active women who are EUM (n=20) or HC users taking or administered COCP (n=20), implants (n=20), IUS (n=20), or hormonal injections (n=20). Participants will be aged 18-40 years; have stable body mass (defined as no change in self-reported body mass ≥5% over the previous 3 months); have a BMI between 18 and 30 kg/m^2^; have a regular menstrual cycle of 24-35 days in length; have not been taking any HC in the last 12 months (EUM group); have used the COCP for at least 12 months (COCP group); have used the IUS continuously for at least 2 years (IUS group); have used the implant continuously for at least 12 months (implant group); or have used the hormonal injection continuously for at least 2 years (injection group). Participants will be excluded if they have diagnosed premature ovarian insufficiency; are pregnant; are less than 2 years post partum; have given birth to more than 2 children; demonstrate evidence of disordered eating (defined as ≥20 on the Eating Attitudes Test-26 items) or have a self-reported eating disorder; report menstrual disturbance (amenorrhea or oligomenorrhea: <9 menstrual cycles in previous 12 months); are a habitual smoker (defined as ≥10 cigarettes per day); are taking any medication known to affect bone or calcium metabolism (eg, treatment for thyroid disorders); have a self-declared history of heart, liver or kidney disease, diabetes or thyroid disorder; self-report a bone injury in the previous 12 months; or have a total 25-hydroxyvitamin D (25(OH)D)<30 nmol/L at prescreening. Finally, any participants not in the injection group who report a history of using the hormonal injection will also be excluded from participation. We will aim to recruit matched sample sizes; however, some HC options are less common, and the study may be unable to achieve the desired sample size. Researchers have stated an end point for data collection of August 2024, giving 2.5 years of recruitment. If any group is underpowered, the sample achieved will be presented to mitigate influences from different time periods. An overview of the study schedule is illustrated in Figure 1; proposed biochemical markers of reproductive health and bone health are listed in Table 1.

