**Calcium**				
	^44^Ca:^42^Ca ratio	4	2	1
	Albumin-adjusted calcium	4	2	1
	Ionized calcium	4	2	1

^a^EUM: eumenorrheic.

^b^COCP: combined oral contraceptive pill.

^c^HC: hormonal contraceptive.

^d^Other HCs include the hormonal injection, hormonal implant, and hormonal intrauterine system.

All participants will attend a prescreening visit to confirm eligibility and to complete familiarization with the muscle strength and functional movement testing protocols. Thereafter, the EUM group will attend the laboratory on 4 occasions, COCP users will attend the laboratory on 2 occasions, and LARC users on 1 occasion (Figure 1). The first visit for the EUM group will be scheduled on day 2 of the menstrual cycle (ie, the second day of the menstrual bleed), according to the predictions based on their cycle length (see the *Menstrual Cycle Tracking* section). As the predictions may not be exact, the first day of the menstrual bleed will be recorded, and we will accept participant testing between day 1 and day 3 of their menstrual bleed. The second visit will be scheduled at the midpoint between day 1 of the menstrual cycle and predicted ovulation. The third visit will be scheduled to coincide with ovulation, predicted from the first day of menses and then determined in *real time* from a urine test for ovulation (LH stick, Clear Blue Advanced Digital) on the days around predicated ovulation. The final visit will be scheduled between ovulation and menstruation (for a 28-day cycle, day 21) as determined by the fertility tracker. Study visits will be scheduled on days 21 (end of active pill phase) and 28 (end of pill-free week) for COCP users (Figure 1B) and at one point in time for hormonal implant, IUS, and hormonal injection users (not represented in Figure 1).

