#### Functional Movement Testing

Participants will perform a single-leg drop to evaluate knee and ankle stability. From a raised platform, participants will stand on one leg with their arms crossed across their chest and “hop off” the platform, landing on the same leg. A total of 3 “hops” will be performed on each leg, with stability assessed using the qualitative assessment of single leg loading [33]. The frontal plane projection angle will be calculated by measuring the angle between the line from the proximal thigh to the midpoint of the knee joint and the line from the knee joint to the midpoint of the ankle, at the frame corresponding to maximum knee flexion [34].

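### A single trained observer limits between-rater variability in the video-scored single-leg drop, but does not address expectation linked to contraceptive group or cycle phase; masked scoring of coded, shuffled clips would reduce it

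*Protocol article*

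**What the plan says.** The Functional Movement Testing section defines two outcomes from the single-leg drop. One is a landing score, "with stability assessed using the qualitative assessment of single leg loading". The other is the frontal plane projection angle, built from segment midpoints "at the frame corresponding to maximum knee flexion". Both require judgement by whoever scores them.

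The Limitations section describes functional movement as "visually assessed from the location of the midpoint of the knee and ankle using video footage", allows that observer bias is possible, and gives one safeguard: "this bias will be minimized by using a single trained observer". The sentence that follows reads "Investigators will also be involved in the testing of all study participants and will not be blinded to HC groups".

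The number of recording sessions depends on the group: "the EUM group will attend the laboratory on 4 occasions, COCP users will attend the laboratory on 2 occasions, and LARC users on 1 occasion" (Methods, visit schedule after Table 1). The article mentions no coding, masking or random ordering of clips. It does not say who the single observer is.

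**The concern.** The safeguard does not match the bias it is said to minimize. Having one observer is a measure for consistency. Observer bias in a comparative study does harm when the scorer knows, or can guess, which group or phase is on screen and scores accordingly. A single observer leaves that route open, and any such tendency then applies to every clip.

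At stake is how the drop-landing results are read. Musculoskeletal performance across the cycle and musculoskeletal function by contraceptive use fall under the primary aims, and the findings are meant to inform thinking on injury risk. The planned covariance analysis, paired *t* tests and mixed model cannot separate a scoring shift that tracks group or phase from a real effect. A reader who accepts that the bias has been minimized would give these outcomes more weight than the design supports.

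**Working it through.** **What one observer does and does not remove.** Write a score as true value + rater offset + shift linked to known group or phase + noise.

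- Rater offset: with one observer it is the same for every clip and cancels in any contrast.
- Group- or phase-linked shift, *b*: it does not cancel. A contrast between two conditions scored with shifts *b*₁ and *b*₂ is off by *b*₁ − *b*₂, however many observers share that expectation.
- Training may reduce landmark-placement error, but it does not remove knowledge of the group.

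**Inputs for an illustration.** The article gives no figure for scoring bias, so there is no figure of its own to reproduce.

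- From the article: 20 women per group and five groups (Recruitment); two-sided α of 0.05; an omnibus test followed by Bonferroni-corrected post hoc *t* tests (Statistical Analyses).
- Assumed: a group-linked shift *b* of 0.2 to 0.5 SD, no true difference, and correction over all pairs, 5 × 4 / 2 = 10, so 0.05 / 10 = 0.005 per pair.

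**Formula.** For one 20 versus 20 *t* test, df = 38 and the noncentrality is *b* × √(20/2). The false-positive rate is the probability that a noncentral *t* exceeds the two-sided critical value: 2.024 at α = 0.05 and 2.980 at α = 0.005.

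| Assumed shift *b* (SD) | Noncentrality | Uncorrected, nominal 5% | Ten-pair Bonferroni, nominal 0.5% |
|---|---|---|---|
| 0.2 | 0.632 | 9.5% | 1.4% |
| 0.3 | 0.949 | 15.2% | 2.8% |
| 0.5 | 1.581 | 33.8% | 9.6% |

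The Bonferroni column is for a single pair and ignores the omnibus gate. The correction lowers the absolute rate but does not restore the nominal one: 1.4 / 0.5 is about 3 times, and 9.6 / 0.5 about 19 times. The five-group omnibus *F* with only the eumenorrheic group shifted gives 8.2% at *b* = 0.2 and 30.5% at *b* = 0.5 (covariates ignored).

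**Does removing rater noise help?** Not against this bias. If between-rater differences were an assumed 20% of total variance, removing them rescales *b* = 0.3 to 0.3 / √0.8 = 0.335, and the uncorrected rate rises from 15.2% to 17.9%. A smaller SD makes the same shift easier to detect as a spurious effect.

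**What masking could gain.** The share of the shift removed is not known. If it were 50%, 75% or 100%, the uncorrected rate would fall from 15.2% to 7.5%, 5.6% or 5.0% for *b* = 0.3, and from 33.8% to 12.0%, 6.7% or 5.0% for *b* = 0.5.

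**The case against.** The strongest reply is that the article already discloses both weaknesses, side by side, in its Limitations section. The sentence on the single observer can be read as concerning landmark placement, for which one trained person is a sensible choice, with lack of blinding listed separately and no safeguard claimed for it. This has some force: nothing is hidden. But the sentence names observer bias in general and says it will be minimized, and that claim is too strong on either reading.

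Second, unmasked scoring is inferred. A reader might conclude that the scorer is known to see group and phase. The article does not state this, and clip handling could be set out in a fuller protocol. That stands, so the point rests on the claim made for the safeguard. The Ethical Considerations section does plan pseudonymized raw data, but a participant code is not masked scoring, because it does not hide group, phase or visit from someone who knows the participants.

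Third, a reader might infer that coded clips would remove most of the bias. The documents do not support this. Investigators take part in testing everyone; an observer who is one of them may recognize a woman and recall her contraceptive group. Nor does masked scoring touch unblinded conduct of the test itself. The gain is clearest within a woman, where recognizing her does not reveal which phase or pill phase a clip shows.

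Fourth, the assumed shift has no source in the documents, and the percentages depend on it and on the test chosen. That stands, and they are illustrative only.

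Finally, the reach is narrow. The sample size rests on calcium balance, the cycle-phase hypotheses and the comparisons of users with eumenorrheic women do not name landing scores, and biochemical and imaging outcomes are unaffected.

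**Conclusion.** The point holds in a limited form. The stated safeguard controls between-rater variability and not expectation linked to group or phase, so the claim that it minimizes observer bias should be corrected. That follows from the article's own text and needs no assumed figure.

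The size of the bias, and of the gain from masking, cannot be fixed from the documents. The illustrative range, about 9.5% to 34% uncorrected or 1.4% to 9.6% at the assumed Bonferroni level, rests on an assumed shift of 0.2 to 0.5 SD and an unmasked scorer. It shows that a modest shift would matter at 20 per group. It does not show that such a shift exists. The point concerns the landing score and the projection angle only, and is a worthwhile, inexpensive improvement and no threat to the study as a whole.

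**What to change.** Replace the claim in the Limitations section with wording such as: A single trained observer will score all clips to reduce between-rater variability. Clips will be exported under random codes, shuffled across participants, groups, phases and visits, and scored without access to group, phase or visit; the key will be held by another member of the current team. Residual bias from recognition of participants, and unblinded conduct of the test, remain as limitations.

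Clips should not be scored participant by participant: with four, two or one sessions depending on the group, the number of clips per woman would itself reveal the group or narrow it down.

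The cost is file renaming and key-keeping, plus a short delay while clips accumulate for shuffling. No extra assessor is needed. Footage already recorded can be rescored in the same way if it has been kept. If masked scoring is not adopted, the section should say plainly that expectation bias remains.

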### Future Directions

The research findings are expected to support the education of women in the military and policy for HC choices. The authors also anticipate identifying additional research needs for the wider impacts of long-term HC use. Investigating injury risk in association with HC use or the impact of HCs during arduous training would be particularly relevant in a military setting. These data also have important implications for exercising women in the general population. An exploration of the lasting effects post-discontinuation of HCs focused on musculoskeletal health and fertility would enhance the research in this field.

### Dissemination Policy

The trial results will be reported to the Ministry of Defence upon completion of all data collection and analysis. The evidence provided by this study will inform servicewomen of the effects of different HC options on their physical strength and performance and guide the decisions of health care professionals when prescribing HCs. With the approval of the Ministry of Defence, the results will be published in several formats, including, but not limited to, peer-reviewed journals, press releases, and conferences.

## Abbreviations

25(OH)D: hydroxyvitamin D
aBMD: areal bone mineral density
COCP: combined oral contraceptive pill
CV: coefficient of variation
DXA: dual-energy x-ray absorptiometry
EUM: eumenorrheic
HC: hormonal contraceptive
HRpQCT: high-resolution peripheral quantitative computed tomography
IGF-I: insulin-like growth factor I
IUS: intrauterine system
LARC: long-acting reversible contraceptive
LH: luteinizing hormone
pQCT: peripheral quantitative computed tomography
